## Abstract

**Background:**

Urinary tract infection (UTI) is a common infection in primary care and is the second leading reason for prescription of antibiotics in Denmark. The diagnosis is often based on symptoms and urine dip-stick, which has limited validity, causing the risk of unnecessary antibiotic prescription. Additionally, with increasing antibiotic resistance, the risk of choosing an antibiotic to which an infecting pathogen is resistant is rising. Combined point-of-care-tests (POCT) for urine culture and susceptibility testing have been developed and validated for primary care, and performing such a test in all patients with suspected UTI in primary care seems rational in order to reduce the use of inappropriate antibiotics. However, the clinical effect of the culture and susceptibility test has not yet been investigated. This study aims to investigate whether POCT urine culture and susceptibility testing decreases the inappropriate use of antibiotics and leads to faster patient recovery.

**Methods/design:**

Randomized controlled open label trial of two diagnostic approaches. 750 patients with symptoms of uncomplicated UTI, consecutively contacting their general practitioner (GP), randomized to either POCT urine culture and susceptibility testing and targeted treatment or POCT urine culture without susceptibility testing and empirical treatment. Treatment is started when the POCT is read. The two groups are compared with regard to appropriate choice of antibiotics, clinical remission, and microbiological cure rates.

**Discussion:**

The results of this study may provide important evidence to recommend POCT culture and susceptibility testing in all patients with suspected uncomplicated UTI. This could become an additional strategy to fight antibiotic resistance.

**Trial registration:**

ClinicalTrials.gov NCT02323087.

## Background

Antibiotic resistance is rapidly spreading, making it one of the most serious threats to human health. The World Health Organization has stated that a post-antibiotic era is a very real possibility and that urgent actions are needed in order to maintain the effect of antibiotics [1].

Primary health care in Denmark is responsible for about 90 % of all redeemed prescriptions of antibiotics, and it is known that a high out-patient consumption of antibiotics leads to high levels of resistance [2, 3]. Thus, a cornerstone in the efforts to reduce antibiotic resistance is to reduce and improve prescription of antibiotics in primary health care.

In 2008, 1.8 % of all patients consulting their GP in Denmark were diagnosed with a UTI [4]. Resistant strains of *E. Coli*, which is the causative organism in 70–80 % of all UTIs, are spreading world-wide [5, 6]. In Denmark, 33–40 % of *E. Coli* isolated from urine samples from primary care are resistant to sulfamethizole and 6–10 % to pivmecillinam, which account for about 80 % of all antibiotic treatments of adults with UTI in primary care in Denmark [3, 7]. It is, therefore, critical that a UTI is treated only when clinically indicated and using an appropriate antibiotic, i.e., one to which the infecting pathogen is susceptible, taking into account the use of first-line agents over second-line agents.

Urine culture is necessary to accurately determine if a patient has a UTI since other tests have limited predictive values in primary care and treating based on symptoms can cause up to 50 % being inappropriately treated [8, 9]. Susceptibility testing adds the advantage to predict whether a first-line antibiotic can be expected to eliminate the infecting pathogen. However, delaying treatment for several days while waiting for the results of the susceptibility test cannot be justified as symptoms are painful and affect quality of life [10, 11]. Point of care test (POCT) culture and susceptibility testing provides the result within 24 h, and can, therefore, be used to target individual therapy without compromising patient welfare. Inappropriate antibiotic prescribing can be partly avoided by performing a POCT culture since this will assumedly eliminate treatment of patients without bacteriuria. However taking into account the above-mentioned resistance rates in *E. Coli* and for example enterococci being inherently resistant to both antibiotics, this could result in about 20–30 % inappropriate antibiotic prescriptions for UTI. Adding susceptibility testing to the POCT should raise the appropriate antibiotic prescriptions above 90 %.

This study aims to answer the questions: 1) Does POCT urine culture and susceptibility testing decrease the use of inappropriate antibiotics, and 2) Does targeted therapy improve clinical outcomes in patients with suspected uncomplicated UTI in general practice when compared to POCT urine culture without susceptibility testing? We hypothesize that the use of POCT susceptibility testing improves the following outcomes: Appropriate choice of antibiotic, clinical remission, and microbiological cure rate.

## Methods

### Study design

Randomized controlled open label trial of two diagnostic approaches in a primary care setting.

### Recruitment process

General practitioners (GPs) 200 general practices in the Copenhagen area will be contacted by letter with the aim of recruiting 50 GPs. All GPs will receive relevant training in the use of POCT culture and susceptibility testing, and their skills will be validated using an online test on how to read the POCT.

#### Patients

Patients presenting with symptoms of UTI will be recruited at the general practice during consultation. To ensure interpretation of POCT within 24 h, only patients contacting practice from Monday to Thursday will be included. Each GP will recruit and randomize 15 patients.

#### Inclusion criteria

Female adult patients, 18 years or older, presenting at their GP with dysuria, frequency or urgency, which has been present for 7 days or less, and for which the GP suspects uncomplicated UTI (including recurrent UTI, uncomplicated diabetes mellitus defined as orally treated, well regulated and without secondary complications, and elderly patients). Patients should be able to deliver a mid-stream urine sample, to provide informed consent, and should be willing and able to fill out a symptom diary.

#### Exclusion criteria

Negative dip-stick analysis on leucocytes and nitrites (to reduce the number of negative cultures)Complicated UTIKnown pregnancySevere systemic symptoms, high fever, flank painRecent bladder surgery (within past 4 weeks)Urinary tract abnormalitiesSerious systemic diseaseLife-threatening cancerInsulin-dependent diabetesLong-term corticosteroid treatmentOther conditions with compromised immunityFormer participation in the studyPatients presenting on a Friday (since POCT is read after 24 h)

#### Randomization and groups

The patients are block randomized in blocks of 10 to ensure approximately equal sizing of the groups. The randomization group for each patient is placed in a sealed envelope which is opened either during or after consultation.For the intervention group, POCT culture and susceptibility testing is performed. Treatment is based on the result of the susceptibility test and clinical guidelines.For the control group, POCT culture without susceptibility testing is performed, and treatment is based on clinical guidelines.

### Informed consent

All patients receive oral and written information before signing informed consent forms.

#### Screening logs

All participating general practitioners, secretaries, and nurses will be asked to maintain an anonymous screening log of all patients fulfilling the inclusion criteria in the inclusion period. This will be used to assess selection and its effect on the study results and for the attrition flow chart.

### Data collection

#### Case-report form

After oral and written information about the project and written consent to enrollment, the GP will take a structured history and fill out a case report form. Data from day 1 consist of:Name and social-security numberDrug allergiesDiabetesNumber of UTIs within past yearSymptoms of UTIDysuriaFrequencyUrgencyDuration of symptomsRandomization group

The patients are asked to contact the GP the next morning by telephone or e-mail for treatment. The patients are also asked to contact the GP if symptoms persist after 4–5 days. The GP can advise on painkillers if necessary.

The next day, the GP will read the plate and inform the patient about the result and potential treatment with antibiotics. The GP will complete the case report form including the following data:Reading of culture plateNo significant growth of uro-pathogensSignificant growth of at least one uro-pathogenInconclusiveFor identified uro-pathogen(s):SpeciesAmount in cfu/mLResistance pattern towards trimetroprim, sulfamethizol, ampicillin, nitrofurantoin, and pivmecillinam (intervention group)Treatment:Name, dose, and duration of antibiotic

#### Symptom diary

The patients are asked to compile and return a paper symptom diary. Through personalized text messages, they are reminded on day 3 to fill out the diary and on day 7 to send it to the Section of General Practice, University of Copenhagen. If they have not sent the diary on day 10 or do not have a cell phone, they receive a phone call. The diary has been face- and content validated through focus groups and personal interviews. The scales for symptom severity, bothersomeness and impact on daily activities are currently under psychometrical validation using the partial credit Rasch model for polytomous items. The secondary outcome of clinical cure is measured using a single item where the patient by the end of each day answers if her symptoms of urinary tract infection are completely gone. The scales for symptom burden are not a part of the secondary outcome but serves to improve the patient’s evaluation of her own cure.

The diary measures:Employment status, job and number of employeesUse of medication other than antibiotics and painkillersSymptom severity on day 1–7Symptom bothersomeness on day 1Impact on daily activities on day 1Use and possible change of antibiotics on day 1–7Use of painkillers on day 1–7Re-consultation with their GP/out-of-hour service on day 1–7Sick-leave on day 1–7Day of becoming symptom-free

#### Urine samples

A mid-stream urine sample from the day of consultation will be divided in two. One part is sent to the local microbiological department, and the other part will be examined at the general practice using the POCT. On day 14 another urine sample will be sent to the local microbiological laboratory for culture.

#### Microbiological analyses performed at the microbiological laboratory– Gold standard

A mid-stream urine sample from day 0 to day 14 are analyzed at the local microbiological laboratory. The sample from day 0 serves as a quality control of the culture and susceptibility testing performed in general practice. The sample from day 14 is the microbiological outcome measure. The samples are transported to the microbiological laboratory in Urine-Monovette® (Sarstedt) containing boric acid to stabilize the bacterial count.

At the microbiological laboratory urine sample are dispersed on Inoqul A™ Bi-plate (CHROMagar and blood agar) with 10 μL on each half of the agar. The susceptibility pattern is determined on Mueller Hinton agars with disks containing mecillinam, cefpodoxim, cefuroxim, gentamicin, piperacillin + tazobactam, meropenem, ampicillin, nalidixic acid, trimethoprim, nitrofurantoin, sulfamethizol, and vancomycin. All samples are quantified. If the bacterial count on the two agars on Inoqul A™ differs with more than a factor 10, the procedure is repeated.

Significant growth is defined as growth of ≥10^3^ colony forming units per millilitre (cfu/mL) for *E. coli* and *S. saprofyticus*, ≥10^4^ cfu/mL for other typical uro-pathogens and ≥10^5^ cfu/ml for possible uro-pathogens following current consensus [12]. All pathogens with significant growth are identified and susceptibility pattern determined. Any pathogen growing at least 10^3^ cfu/ml, unless the above mentioned criteria are fulfilled, is classified as contamination, and in these cases the susceptibility pattern is not determined. Insignificant growth is defined as ≤ 10^2^ cfu/mL or less. Susceptibility pattern is determined according to EUCAST and NordicAST recommendations. The internal quality control is performed measuring inhibition zones on chosen reference strains from American Type Culture Collection (ATCC) and National Collection of Type Cultures (NCTC).

#### Microbiological analyses performed on-site at the general practice

##### Culture (control group)

Point-of-care culture will be performed using ID Flexicult™ (SSI DIagnostica, Denmark) which is a chromogenic agar plate for identification and quantitation of urinary tract pathogens. The sample is seeded with a 10 μL inoculation needle, the lid is applied, and the agar plate incubated upside down at 35 °C overnight. The plate is read the next day. If it is positive, no further incubation is needed, if it is negative, incubation is continued until 24 h after inoculation. The bacterial identification is based on colony color and size. The agar plate can be seen on the right side of Fig. 2.

##### Culture and susceptibility testing (intervention group)

Urine culture and susceptibility testing will be performed on the intervention group by means of a POCT, the FLEXICULT™ SSI-Urinary Kit (SSI Diagnostica, Denmark). The kit is a chromogen agar in an ordinary Petri dish, but with higher sides. The Petri dish is divided into 6 compartments: 1 large compartment for quantitative analysis and 5 smaller compartments for susceptibility testing. The agar in each of the smaller compartments contains 1 of 5 antimicrobials: trimethoprim, sulfamethoxazole, ampicillin, nitrofurantoin, and mecillinam. The agar plate can be seen on the left side of Fig. 2.

The agar plate is flooded with the urine specimen for a couple of seconds and then incubated at 35 °C over night. The plate is read on the following day.

As the concentrations of the antimicrobials in the 5 smaller compartments are adjusted in accordance with breakpoints, growth on these compartments indicates resistance of the pathogen in question and hence a potential risk of treatment failure.

Figure 1 illustrates the data collection process and Fig. 2 explains the study design and the difference between the intervention and control arm.

**Fig. 1 Fig1:**
[figure not shown]
Flow-chart for data collection. POCT: Point of care test. This refers both to POCT culture and POCT culture and susceptibility testing. GP: General practitioner

**Fig. 2 Fig2:**
[figure not shown]
Study design of randomized controlled trial. The figure shows the study design with the intervention arm on the left and the control arm on the right. The shown agars are the ones used in the trial, courtesy of SSI Diagnostica

### Definition of outcomes

#### Primary outcome

The proportion of patients receiving appropriate antibiotic treatment on the day after consultation. Data obtained from case-report form.

Appropriate antibiotic treatment is defined as receiving a first-line antibiotic to which the infecting organism is susceptible, if there is significant growth in the gold standard or receiving any antibiotic to which the infecting organism is susceptible if there is significant growth in the gold standard if the patient is allergic or the infecting organism is resistant to all first-line antibiotics or not receiving an antibiotic if there is no significant growth in the gold standard. The definition is illustrated in Fig. 3.

**Fig. 3 Fig3:**
[figure not shown]
Short title of figure: Flow-chart for primary outcome and definition of appropriate and inappropriate choice of treatment

#### Secondary outcomes

The proportion of patients who are asymptomatic on the fourth day of treatment (clinical cure) defined as the patient stating, her symptoms are completely gone regardless of symptom score. Data obtained from symptom diariesThe proportion of patients with no significant bacteriuria on day 14 (bacteriological cure). Data obtained from control urine sample

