### Secondary outcomes

#### Clinical remission

McNulty and Ferry reported clinical cure rates of 69 % on day 5 after targeted treatment with trimethoprim and 44 % on day 5 empiric treatment with pivmecillinam respectively in patients with uncomplicated UTI [13, 14]. Assuming a cure rate of 60–70 % on the fourth day of treatment (day 5) in the intervention group, a difference of at least 15 percentage points could be detected with the chosen sample while accounting for a 25 % drop-out on clinical follow-up.

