### Statistical analysis

Comparison of the two randomization groups for both the primary and the secondary outcomes will be done by means of an odds ratio (OR) from a logistic regression model; clustering within practices is adjusted for by generalized estimating equations (GEE). Analyses will be performed intention-to-treat, i.e., the patients are analyzed in the groups they are randomized to regardless of the treatment they actually received. Effect modification – whether the effect of the intervention differs between subgroups in the data – will be investigated for GP factors (organization of practice, performance in reading the POCT), patient factors (age, concurrent illness, socio-demographic data, initial symptom score) and microbiological factors (amount and species). If a sufficient sample is obtained, sub-group analysis will be performed for patients with diabetes, elderly patients and patients with recurrent UTI since these groups are expected to benefit the most from the intervention. In an additional analysis of the primary outcome, the group inappropriately treated will be divided into under-treated and over-treated and analyzed in multinomial logistic regression models. Comparison of cure-rates will be done with Kaplan-Meier curves and log-rank tests. A P-value of 0.05 will be considered significant. Analyses will be performed with SAS v9.4.

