## Discussion

In Denmark, POCT combined culture and susceptibility testing has been in use for decades, and the use has increased since introduction of the FLEXICULT™ SSI-Urinary Kit. Despite this popularity no clinical trials have yet validated its impact in clinical practice. This study will investigate the effect of POCT susceptibility testing on appropriate choice of antibiotics and on clinical and microbiological cure in patients with uncomplicated UTI in primary care in Denmark.

The clinical effect and cost-effectiveness of POCT culture and susceptibility testing in UTI is currently being investigated by another research group [15]. Although both studies aim at investigating the effect of the Flexicult on the appropriateness of antibiotic use and the impact on patient outcomes, there are at least three important differences. Firstly, in the study by Bates et al., the effect of combined culture and susceptibility testing is compared to various forms of standard care in a four-country multicenter setting. The focus of the present study is narrower, specifically aiming at determining the value of the susceptibility component compared to culture alone in a single region in Denmark. Secondly, all GPs in this study are experienced users of POCT susceptibility testing, and their skills are validated before enrollment of patients as described under the recruitment process, thus inter-practice variation is minimized. Thirdly, in this study, both groups will have treatment delayed until a positive culture is obtained, thereby minimizing the number of culture-negative patients receiving inappropriate antibiotic treatment.

We have chosen to include patients with diabetes, recurrent UTI and elderly patients when they are otherwise healthy and can be safely included. In the analysis, they are investigated for effect modification and, if the sample allows it, they are analyzed separately, since they could be expected to benefit more from the intervention than other groups.

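### The definition of bacteriological cure counts women who had no bacteriuria to cure, and clinical cure is tied to a treatment day that untreated women do not have

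*Protocol article*

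**What the plan says.** All references are to the Protocol article.

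- Secondary outcomes: clinical cure is "The proportion of patients who are asymptomatic on the fourth day of treatment (clinical cure", and bacteriological cure is the "proportion of patients with no significant bacteriuria on day 14 (bacteriological cure". Both are proportions of patients. Neither is limited to women who were treated or who had growth at baseline.
- Primary outcome: one way to be treated appropriately is "not receiving an antibiotic if there is no significant growth in the gold standard". The Discussion adds that "both groups will have treatment delayed until a positive culture is obtained". The dip-stick exclusion criterion is meant to lower the number of negative cultures, not to remove them. Uninfected and untreated women are therefore part of the planned population.
- Statistical analysis: the comparison covers primary and secondary outcomes by intention to treat, so that "the patients are analyzed in the groups they are randomized to regardless of the treatment they actually received".
- Clinical remission (sample size): "Assuming a cure rate of 60–70 % on the fourth day of treatment (day 5) in the intervention group". This is where a calendar day is attached to the clinical-cure time point.
- Symptom diary: at the end of each day the patient "answers if her symptoms of urinary tract infection are completely gone". The item does not depend on treatment.
- Bacteriological cure rate (sample size): the planning figure is about 90 % at day 8–10 with empiric antibiotics, and no significant difference is expected.

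**The concern.** Cure presupposes something to cure. As defined, a woman with no significant growth on day 0 and none on day 14 is a bacteriological cure. Such women raise the reported rate in an arm whenever they are clear on day 14 more often than infected women are. They also dilute the contrast, because susceptibility results cannot guide drug choice where there is no pathogen. The result then does not correspond to the 90 % planning figure, which describes women given antibiotics.

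For clinical cure the difficulty is the clock. A woman who never starts an antibiotic has no fourth day of treatment, so the definition read alone gives her no assessment day. At stake are the size and meaning of the two secondary effects, and whether different analysts would assign untreated women the same day.

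**Working it through.** **The plan's own figure.** The Clinical remission section says at least 15 points can be detected after 25 % drop-out, with 60–70 % cure in the intervention arm. Evaluable women: 750 × 0.75 = 562.5. With two equal arms, a two-sided 0.05 test and no clustering, power for 15 points is 95–96 %, and the smallest difference detectable with 80 % power is 11.3–11.8 points. From 600 × 0.75 = 450 women, the figures are 89–91 % and 12.7–13.2 points. The statement is therefore met as a lower bound under individual randomisation. The plan gives no power level or clustering rule for it, so it cannot be reproduced exactly. I apply no design effect below.

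**Dilution formula.** Let π be the share with significant day-0 growth. In each arm, P(all) = π × P(growth) + (1 − π) × P(no growth). If P(no growth) is the same in both arms, the overall difference is π × the difference in infected women. The documents do not give π; I assume 0.5–0.8.

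**Bacteriological outcome.** Inputs: control 90 % in infected women (the plan's figure); intervention 95 % (assumed); women without day-0 growth clear on day 14 in 100 % or 95 % (assumed); 562 evaluable (assuming the same 25 % loss).

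| π | All women, 100 % clear | All women, 95 % clear | Difference (points) | Power, all women (100 % / 95 % clear) | Power, day-0 growth only |
|---|---|---|---|---|---|
| 0.8 | 92.0 v 96.0 | 91.0 v 95.0 | 4.0 | 52 % / 46 % | 52 % |
| 0.6 | 94.0 v 97.0 | 92.0 v 95.0 | 3.0 | 40 % / 30 % | 41 % |
| 0.5 | 95.0 v 97.5 | 92.5 v 95.0 | 2.5 | 34 % / 23 % | 36 % |

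The first entry is 0.8 × 90 + 0.2 × 100 = 92. If women without day-0 growth are always clear on day 14, almost no power is lost, and the harm is the inflated rate and the label. Power is lost when some of them have bacteriuria by day 14.

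A second example with lower rates: π = 0.65, 85 v 90 % in infected women, 95 % clear in the others.
- All women: 0.65 × 0.85 + 0.35 × 0.95 = 0.885, against 0.65 × 0.90 + 0.35 × 0.95 = 0.9175. Standardised difference: 0.0325/√0.1775 = 0.077.
- Day-0 growth only: 0.05/√(0.2175/0.65) = 0.086, about 12 % larger.

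**Clinical outcome.** Inputs: 15 points in infected women (60–70 % in the intervention arm), none in the others (40 % or 60 % cured in both arms, assumed), 562 evaluable.

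| π | Difference, all women (points) | Power, all women | Power, day-0 growth only |
|---|---|---|---|
| 0.8 | 12.0 | 81–84 % | 89–91 % |
| 0.7 | 10.5 | 70–73 % | 85–87 % |
| 0.6 | 9.0 | 57–59 % | 79–82 % |
| 0.5 | 7.5 | 43–45 % | 71–74 % |

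With similar variances the test statistic in infected women is larger by 1/√π: 1.12 at 0.8 and 1.41 at 0.5.

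**Day numbering.** The Case-report form section labels the consultation data day 1; the laboratory section labels the consultation sample day 0. Treatment starts the day after consultation. Counting consultation as day 1, treatment starts on day 2 and its fourth day is day 5, as the Clinical remission section says. Counting consultation as day 0, the fourth day would be day 4.

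**The case against.** A reader might infer that clinical cure will be analysed in treated women only, and so compares subsets formed after randomisation by two different culture plates, against the intention-to-treat rule. The documents do not support this. The denominator is patients, the sample-size text supplies day 5, the diary item is answered daily whatever the treatment, and intention to treat is stated for the secondary outcomes. What remains is that the definition itself omits the day.

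It can also be argued that the all-women analysis is the right one. The study question concerns suspected infection, and the GP cannot separate infected from uninfected women when choosing the test. Randomisation balances culture-negative women in expectation, so the comparison is not biased. This stands, and it is why the all-randomised analysis should be kept.

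The two arms use different plates and inoculation methods, so unnecessary treatment of uninfected women could differ by arm. The dilution formula would then not be exact, and an analysis of infected women alone would hide that effect. This too supports reporting both.

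The plan does examine effect modification by amount and species of bacteria, but that does not set the population for either cure outcome. An article may leave denominators to the full protocol or analysis plan, which are not shown. Even so, the published definition calls the day-14 result cure without requiring infection. Finally, the growth share is assumed: at 0.8 the loss for clinical cure is modest, and the dip-stick exclusion pushes the share upwards.

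**Conclusion.** The point holds as a should-fix on two secondary outcomes; the primary outcome is unaffected. Bacteriological cure includes women with nothing to cure. That dilutes the contrast, raises the rates where uninfected women are clear more often than infected women, and does not match the treated-women planning figure. Clinical cure has a time anchor that is undefined for untreated women, although a usable day appears elsewhere in the article.

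The all-women difference is π times that in infected women: 2.5–4 points for 5, and 7.5–12 for 15, over π = 0.5–0.8. This assumes no effect in uninfected women. The power figures also assume 562 evaluable women and no clustering. It would go too far to call either outcome invalid: the harm is dilution, an unclear day and a misleading label, not bias.

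**What to change.** 1. In Secondary outcomes, define clinical cure as the patient reporting all symptoms gone on diary day 5, with the consultation day as day 1, for every randomised woman whether treated or not. Reconcile the day numbering between the Case-report form and laboratory sections.
2. Call the all-women day-14 outcome 'no bacteriuria'.
3. Keep the all-randomised intention-to-treat analysis. Alongside it, pre-specify an analysis of both cure outcomes by randomised group in women with significant growth in the day-0 laboratory culture, whatever the point-of-care plate showed or drug was given. That sample is taken at consultation, before treatment, and is cultured by the same method in both arms, so the restriction does not select on the treatment decision.

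Cost: revised outcome wording, one more analysis per secondary outcome, and fewer women in the culture-positive analysis. No new data are needed, as the daily diary item and both laboratory cultures are already collected.
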